## Abstract

**Background:**

The efficacy of the classical treatment modalities surgery and radiotherapy in the treatment of aggressive fibromatosis is presently disputed and there is a shift towards a more conservative approach. The aim of the present study is to objectify tumor growth in patients with extra-abdominal or abdominal wall aggressive fibromatosis, while adhering to a “watchful waiting” policy. Other objectives are to investigate quality of life and to identify factors associated with tumor growth, in particular the relation with the presence of a CTNNB1-gene mutation in the tumor.

**Design and methods:**

GRAFITI is a nationwide, multicenter, prospective registration trial. All patients with extra-abdominal or abdominal wall aggressive fibromatosis are eligible for inclusion in the study. Main exclusion criteria are: history of familiar adenomatous polyposis, severe pain, functional impairment, life/limb threating situations in case of progressive disease. Patients included in the study will be treated with a watchful waiting policy during a period of 5 years. Imaging studies with ultrasound and magnetic resonance imaging scan will be performed during follow-up to monitor possible growth: the first years every 3 months, the second year twice and the yearly. In addition patients will be asked to complete a quality of life questionnaire on specific follow-up moments. The primary endpoint is the rate of progression per year, defined by the Response Evaluation Criteria In Solid Tumors (RECIST). Secondary endpoints are quality of life and the rate of influence on tumor progression for several factors, such as CTNNB1-mutations, age and localization.

**Discussion:**

This study will provide insight in tumor behavior, the effect on quality of life and clinicopathological factors predictive of tumor progression.

**Trial registration:**

The GRAFITI trial is registered in the Netherlands National Trial Register (NTR), number 4714.

## Background

### Biological behavior

Desmoid-type fibromatoses are rare, non-metastasizing, locally aggressive soft tissue tumors. Aggressive fibromatoses can be located in every part of the body and are classified as extra-abdominal, abdominal wall or intra-abdominal [1, 2]. The abdominal wall is a predilection site in women of reproductive age [3]. Sporadic onset of the tumor is common, but an association with familiar adenomatous polyposis (FAP) has been documented, in particular in intra-abdominally localized aggressive fibromatoses [4]. The course of the disease is unpredictable and varies between relatively indolent, i.e. stabilization of the tumor, and progressive growth, which may halt spontaneously [5]. The reported frequency of recurrence following local treatment ranges from 5 to 63 % [6].

Genetic markers in tumor tissue have been analyzed, in particular the CTNNB1-gene. CTNNB1-gene encodes beta-catenin, a proto-oncogene involved in cell adhesion and cell transcription. Beta-catenin is a key factor in the Wnt-APC-beta-catenin pathway. On a cellular level the beta-catenin protein level is elevated in these tumors, implicating beta-catenin stabilization as a key factor in the pathogenesis of aggressive fibromatosis [7, 8]. Nuclear overexpression of beta-catenin is a histological condition used in a diagnostic. The diagnostic value is sensitive, but not specific [8–10]. Research on the CTNNB1-gene revealed 3 specific mutations, namely T41A, S45F and 45P [8, 10]. While it is yet unclear how these mutations precisely affect the aforementioned pathway in these tumors, a role in biologic behavior seems natural according to their role in pathogenesis. Several groups have analyzed CTNNB1-mutation and these mutations appear to have a prognostic value in determining the risk of recurrence in retrospective series of surgically treated patients [11–15]. Although Mullen et al. did not find a statistical significant prognostic [15], several other groups reported a higher risk of recurrence for patients with an S45F-mutation [11–13], even in multivariate analysis [12]. In addition, (surgical) trauma and hormones presumably play a role in the genesis of this tumor, as aggressive fibromatosis is known to arise in scars and in fertile females [16].

### Treatment

Treatment of aggressive fibromatosis classically involves surgery, combined with radiotherapy on indication. Literature on the effects of surgery and radiotherapy on the rate of recurrence is conflicting [17–19]. While these effects are still being questioned, treatment policies have recently turned towards a more conservative approach. Nowadays, a watchful waiting approach is being advocated by various authors and is currently the standard in European care [20–25]. Retrospective studies showed that progression usually occurs within 2 years of diagnosis. Fiore et al. [22] reported a median time till progression of 14 months, with 89 % of progression observed within 2 years, while Salas et al. [18] described a median time till progression of 20 months. In addition, these studies have also reported spontaneous regression in up to 18.5 % of the patients [18, 22].

The ability to predict tumor behavior would enable tailoring individual patient treatment. Little is known about tumor growth. Available literature is dated and descriptive, without objective measurements [16].

### Study aim

The GRAFITI study will evaluate a watchful waiting approach as an initial treatment for patients with extra-abdominal or abdominal wall aggressive fibromatosis. The primary objective is to assess tumor progression using the Response Evaluation Criteria In Solid Tumors (RECIST) [26]. We will attempt to identify patient-and tumor characteristics related to growth. A twin study is ongoing in Milan, Italy (NCT02547831). The present study proposal was designed in collaboration with the Italian study group, to facilitate a possible future merger of data.

## Design and methods

### Study design

GRAFITI was designed in collaboration with experts in sarcoma care throughout the Netherlands as a nationwide prospective observational study. All patients with extra-abdominal or abdominal wall aggressive fibromatosis are eligible for participation. Inclusion and exclusion criteria are discussed below. If not included, treatment options will be discussed by the local multidisciplinary teams. Treatment modalities include systemic treatment, surgery and radiotherapy, and individualized treatment will be chosen based on patient characteristics, tumor localization and predicted outcome.

Patients will be treated by a watchful waiting policy and asked to complete quality of life questionnaires. During follow-up, imaging studies will be performed to monitor tumor growth. In case of growth, all treatment options will be evaluated, including continuation of watchful waiting. A switch in treatment strategy will be monitored and reasons for this switch documented (see Fig. 1).

**Fig. 1 Fig1:**
[figure not shown]
Flowchart

### Primary objective

The primary objective is to assess tumor progression in terms of objectifying and monitoring growth during watchful waiting policy as an initial treatment. Ultrasound and MRI imaging will be used to determine tumor size. Tumor behavior will be scored using RECIST. Primary endpoint is the rate of progression per year, which will be measured after 5 years of follow-up.

### Secondary objectives

The secondary objective is to investigate the effect of treatment on the quality of life. During the study period, patients will be asked to complete the EORTC QLQ-C30 questionnaire five times: at inclusion and after 6,12,24 and 60 months. After a switch to active treatment, patients will remain on-study for the questionnaires. The scores will be evaluated and related to treatment policy.

Other objectives are to analyze the value of clinicopathological factors, including CTNNB1-gene mutation, in predicting progression. The reasons and considerations for active treatment will be analyzed in relation to the applicability of a watchful waiting policy.

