### Sample size

Based on the incidence of sporadic aggressive fibromatosis and tumor localization, we expect to include 20 patients annually, we aim to include 100 patients in 5 years. Loss to follow-up or death is not to be expected. Under the most adverse conditions, a progression rate of 50 % would result in a 95 % confidence interval (95 % CI) of 40–60 %. A progression rate of 25 % would result in a 95 % CI of 18–34 %. We consider the presented 95 % CI to be acceptable for the study.

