### Statistical considerations

Statistical analysis will be carried out using IBM SPSS Statistics 21. Radiological measurements will be registered as a continuous variable at ratio. The average progression rate per year will be analyzed using data of all patients. The progression rate per year, defined as increase in size per tumor, using RECIST criteria, with the associated range and confidence interval, will be registered as the primary outcome. The QLQ-C30 questionnaire results in a score to classify the quality of life. This score will be registered as discrete data at ratio scale. If a score cannot be rewarded, the data of the questionnaire will be regarded as missing data. If a score is missing, but later registered scores are available, the later scores will be used in assessment of the quality of life. The overall quality of life will be calculated using data of all patients at the end of follow-up. The median value will be extracted with the associated range.

The possible influence of patient and tumor related factors on the progression rate and the quality of life are analyzed using the Kaplan-Meier method and univariable Cox-regression. Associations between variables will be explored by Chi-square analysis. Multivariate analysis will be performed if possible by means of Cox-regression. Those factors which prove to have statistical significance in univariate analyses, will be included in the multivariate analysis. The considerations for treatment will be categorized and analysis will show the occurrence of specific considerations.

The interim analysis of both primary and secondary parameters will be done after one year of follow-up on 20 patients. The analyses will be the same as described above and will be performed by the principal investigator. For all analyses, two-sided *P <* 0.050 is considered statistically significant.

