In addition, CTNNB1-mutations are found to be a predictive factor for the risk of recurrence following surgery [12–14, 16]. The value of these factors in a postoperative setting cannot be extrapolated to a watchful waiting setting. The present study was designed to evaluate the role of these factors in relation to the progression rate in a watchful waiting setting. This information would help in determining which patients can safely undergo a watchful waiting policy, and which patients would benefit most from active treatment. The ability to predict tumor behavior would enable tailoring individual patient treatment and prevent over-or undertreatment.

The low incidence of aggressive fibromatosis presents a challenge for quality research. Collaborations between specialized institutions is essential. The prospective evaluation of predictive factors in a watchful waiting setting has been initiated by two other research groups. In France, Bonvalot et al. are conducting a similar study (ClinicalTrials.gov identifier NCT01801176). They have finished the inclusion process and are now conducting the final follow-up. In Italy, a similar study is coordinated by [name] et al. (ClinicalTrials.gov identifier NCT02547831). This study is still open and we encourage inclusion. The present study was designed to resemble the French and Italian study, to facilitate a possible merging of the data if the inclusion rate in the studies would be disappointing. Main inclusion and exclusion criteria match for all three studies, though our study also includes patients presenting with recurrent disease.

The occurrence of aggressive fibromatosis has been related to hormonal influences and pregnancy by Häyry and Reitamo et al. [16, 28]. Although hormonal levels and receptors on the tumor have not been investigated, the occurrence of disease among fertile females is very suggestive. A recent study by van Broekhoven et al. evaluated time trends in the Dutch population [29]. Their analysis between incidence and hormonal influences did not show a positive correlation. In an attempt to evaluate the hormonal influence, data on the use of hormonal medication and history of pregnancy will be collected during the present study.

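### The secondary objective is about predicting progression, but the only stated rule for factors is univariate P<0.050 for entry to the multivariable Cox model, which may leave CTNNB1 untested beside age, localization and size

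*Protocol article*

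**What the plan says.** Secondary objectives in the protocol article: "Other objectives are to analyze the value of clinicopathological factors, including CTNNB1-gene mutation, in predicting progression". The Discussion gives the intended use: "This information would help in determining which patients can safely undergo a watchful waiting policy, and which patients would benefit most from active treatment". It adds that predicting tumor behavior would allow treatment to be tailored to the individual.

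Statistical considerations says that the influence of patient and tumor factors on progression is "analyzed using the Kaplan-Meier method and univariable Cox-regression", with a multivariable Cox model if feasible. The rule for building that model is: "Those factors which prove to have statistical significance in univariate analyses, will be included in the multivariate analysis". The threshold is general: "For all analyses, two-sided *P <* 0.050 is considered statistically significant".

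The abstract describes the same endpoint less ambitiously, as "the rate of influence on tumor progression for several factors, such as CTNNB1-mutations, age and localization". The abstract's background and the Study aim section also speak of factors associated with, or related to, growth.

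**The concern.** Predictive value raises two questions: how far a factor separates patients who progress from those who do not, and what it adds to characteristics already known. A P value answers neither. It depends on the number of events as well as the size of the effect.

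The entry rule makes the second question harder to answer. The Discussion names age, localization and size as predictors of recurrence after surgery, so the natural question for CTNNB1 is what it contributes beside them. Under the rule, CTNNB1 is dropped from the joint model if it misses P<0.050 alone. If age, localization or size miss it, CTNNB1 is not adjusted for them. Either way its added value may go unreported, in a study that hopes to inform patient selection.

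**Working it through.** **Inputs.** From Sample size: "we aim to include 100 patients in 5 years", no expected loss to follow-up, and progression rates of 50% and 25%. I read these rates as 50 or 25 patients of 100 with a progression. The Wilson interval reproduces the article's own figures: 50/100 gives 40.4–59.6% (stated 40–60%) and 25/100 gives 17.5–34.3% (stated 18–34%). Marker prevalence p is not given, so p = 20%, 30% and 40% are assumptions.

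**Just-significant hazard ratio.** With d progressions, HR = exp(1.96 / √(d·p·(1−p))). For d = 50 and p = 0.2: d·p·(1−p) = 8, so HR = exp(1.96/2.828) = 2.00.

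**Risk per group.** With proportional hazards, S0, the progression-free proportion in marker-negative patients, solves (1−p)·S0 + p·S0^HR = 1 − d/100. For d = 50, p = 0.2, HR = 2: 0.8·S0 + 0.2·S0² = 0.5, so S0 = 0.5495. Progression is 45% in marker-negative and 1 − 0.5495² = 70% in marker-positive patients.

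**Share of progressors who are marker-negative** = (1−p)·(1−S0) / (d/100). Here 0.8 × 0.4505 / 0.5 = 72%.

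| Progressions | Prevalence (assumed) | Just-significant HR | Risk, negative | Risk, positive | Progressors marker-negative |
|---|---|---|---|---|---|
| 50 | 20% | 2.00 | 45% | 70% | 72% |
| 50 | 30% | 1.83 | 44% | 65% | 61% |
| 50 | 40% | 1.76 | 42% | 62% | 50.5% |
| 25 | 20% | 2.66 | 20% | 45% | 64% |
| 25 | 30% | 2.35 | 19% | 39% | 53% |
| 25 | 40% | 2.23 | 18% | 36% | 43% |

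**Cross-check with 2×2 tables.** I took the smallest excess in marker-positive patients that reaches P<0.05 on chi-square (with and without continuity correction) and on Fisher's exact test. At 20% prevalence this is 15/20 versus 35/80 (35/50 = 70% of progressors marker-negative) or 9/20 versus 16/80 (16/25 = 64%). At 40% it is 26/40 versus 24/60 (48%) or 15/40 versus 10/60 (40%). The pattern is the same.

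**Discrimination.** For a binary marker without censoring, c = 0.5 + p(1−p)·(HR−1)/(HR+1). At 50 progressions this gives 0.5 + 0.16 × 1/3 = 0.55 (p = 0.2) and 0.5 + 0.21 × 0.83/2.83 = 0.56 (p = 0.3). The ceiling for such a marker is 0.5 + p(1−p) = 0.66 and 0.71.

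**Chance that CTNNB1 misses the model.** Assume a true hazard ratio of 2.5, which is not in the article. Power for univariate significance is Φ(ln 2.5·√(d·p·(1−p)) − 1.96). At p = 0.2 this is 74% with 50 progressions and 45% with 25; at p = 0.3 it is 84% and 56%. A marker of that strength would therefore fail to enter in 16–26% of trials with 50 progressions and in 44–55% with 25.

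**The case against.** The strongest reply is that the aim is association and the methods match it. The abstract and the Study aim section are worded that way, and the article elsewhere uses predictive factor loosely, much as one would say risk factor. This has weight, and it is why the mismatch is limited. It does not remove it, because Secondary objectives asks for value in prediction and the Discussion gives that a patient-selection use.

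A reader might infer that the plan will call any factor with P<0.050 predictive. The text does not say so. The significance sentence governs entry to a model, and the Discussion's remarks on selection are conditional hopes, not a decision rule. Kaplan-Meier curves by factor can already supply absolute risks, and a multivariable hazard ratio for CTNNB1, if CTNNB1 enters, would bear on its added contribution.

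The illustration must also be read fairly. For a minority marker of modest effect, most events fall in the larger group. That shows low sensitivity, not absence of predictive value: 70% versus 45% is a 25-point difference. The c-index should be judged against its ceiling as well as against 0.50.

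Finally, a c-index may be left to a fuller document. The point here is not that it is absent. It is that the entry rule which is stated does not serve the stated objective.

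**Conclusion.** The point stands as a limited mismatch in a secondary objective. The primary endpoint and the sample size are not affected. The model-entry rule shows association and may leave CTNNB1 unexamined beside age, localization and size.

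The figures of 61–72% (50 progressions) and 53–64% (25 progressions) of progressors marker-negative hold for a binary marker exactly at the significance threshold, under proportional hazards and an assumed prevalence of 20–30%. At 40% the shares are about 50% and 43%, so it cannot be said without condition that most progressors would lack a significant marker. Nor do the documents support the stronger inferences that significance is the only evidence the analysis will yield, or that the trial answers a different question from the one it sets.

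**What to change.** - Replace entry by univariate significance with a pre-set Cox model containing age, localization, size and primary or recurrent status (Study population already calls for stratification by the last). Fit it without and with CTNNB1.
- Report the adjusted hazard ratio for CTNNB1 with its confidence interval, and the optimism-corrected c-index of both models as a supporting measure only.
- Report progression risk at 2 and 5 years with 95% CI for each factor level, from the Kaplan-Meier curves already planned.
- Base statements on predictive value on these figures and not on P<0.050 alone. Otherwise, word the conclusion as association.

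This needs no new data, only analysis time. The price is wide intervals and a limit on model terms. With one term per factor the model with CTNNB1 has five, so 25–50 progressions give 25/5 = 5 to 50/5 = 10 events per term, and fewer if localization or the three CTNNB1 mutations are entered at several levels. For that reason the c-index difference should not be the sole basis of any conclusion.

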### Study population

The study will take place in the Netherlands. All patients with extra-abdominal or abdominal wall aggressive fibromatosis are eligible for inclusion in the study. Primary and recurrent disease will be included, stratification will be done for analyses.

### Inclusion criteria

Histological evidence of aggressive fibromatosis. Capable to undergo MRI-scans and ultrasounds. Capable to understand and sign informed consent.

### Exclusion criteria

Age <18 years. Personal or family history of FAP. Intra-abdominal tumor localization. Previous treatment for the current manifestation (recurrent lesions without previous treatment are included). Severe pain or functional impairment due to the tumor (as indicated by the patient. The use of painkillers is not an exclusion criterion). Tumor progression leading to mutilation or life/limb-threatening situations, as assessed by the attending physician.

### Sample size

Based on the incidence of sporadic aggressive fibromatosis and tumor localization, we expect to include 20 patients annually, we aim to include 100 patients in 5 years. Loss to follow-up or death is not to be expected. Under the most adverse conditions, a progression rate of 50 % would result in a 95 % confidence interval (95 % CI) of 40–60 %. A progression rate of 25 % would result in a 95 % CI of 18–34 %. We consider the presented 95 % CI to be acceptable for the study.

## Methods

Participation in the study implies that the work-up does not deviate from present common practice. A contrast enhanced MRI-scan (T1 and T2 weighted) is used to determine the precise localization, size and involved structures. Subsequently, and also in line with national guidelines, the patient will undergo an ultrasound-guided, histological needle-biopsy of the soft tissue tumor, with a 14 G needle. Preferably 3 biopsies will be obtained. During the ultrasound, tumor size will be measured in three dimensions. In addition, as part of this study a quality of life questionnaire is completed by the patient.

The follow-up schedule is set for 9 outpatient-clinic visits (see Table 1). During each visit imaging studies will be performed to monitor possible growth. In addition, patients will be asked to complete a questionnaire during 5 follow-up visits. The radiology report of the ultrasound or MRI-scan will specify the maximum diameter in all 3 dimensions and the growth in relation to previous radiological examinations. When ultrasonography suggests tumor progression, an MRI-scan is additionally made as standard care and considered as the golden standard for detecting changes within the tumor.

**Table 1 Tab1:** Follow-up schedule

Assessment	Enrollment	Year 1				Year 2		Year 3–5		
Month		3	6	9	12	18	24	36	48	60
History and Physical examination	x	x	x	x	x	x	x	x	x	x
MRI-scan	x		x		x		x	x		
Ultrasound	x	x		x		x			x	x
QoL questionnaire	x		x		x		x			x

In case of tumor progression, the patient will be re-evaluated. If the patient is still eligible, watchful waiting policy will be continued. If not, local or systemic treatment will be started and considerations to switch treatment strategies will be documented.

After inclusion of all patients, pathology specimens will be collected by one pathology laboratory and CTNNB1-gene analysis will be performed for all patients. If CTNNB1-mutation status is already known, this procedure will not be repeated.

